### Hypothesis

Primary Endpoint: We hypothesize that patients undergoing a pre-operative neuromuscular training in addition to the educational program will be significantly quicker in performing the Chair Stand Test (test of lower extremity function) compared with those receiving the educational program alone immediately after the intervention and after TKR surgery.

Secondary Endpoints: We hypothesize that patients undergoing a pre-operative neuromuscular training in addition to the educational program will have a greater improvement in function and pain (KOOS subscales) compared with those receiving the educational program alone immediately after the intervention and after TKR surgery.

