**Figure 1 F1:**
[figure not shown]
Flow chart of research design.

Outcomes are measured at baseline (6–12 weeks pre-operative: primary and secondary endpoints), 1 week pre-operative (after the intervention: primary and secondary endpoints), 6 weeks after surgery (secondary endpoints only), 3 months after surgery (primary and secondary endpoints) and 1 year after surgery (secondary endpoints only).

Prior to the baseline assessment eligible patients receive an information package on the study. The package includes detailed information, including their rights when participating in a research project and a written informed consent form. Ethic approval was granted by the Ethics Committee of the Cantons Aargau and Solothurn, Switzerland, approval number 2009/012.

Reporting of the RCT follows the recommendations of CONSORT guidelines for reporting of clinical trials and will be based on intent-to-treat [21]. In addition, a per-protocol analysis will be performed.

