### Sample size calculation

The sample size calculation is based on the primary endpoint - the Chair Stand Test. We assume that the mean difference in change over time between groups is 7.3 seconds (corresponding to means of 8.3 and 1.0, respectively) and the common within-group standard deviation is 7.3. This effect was selected based on pilot data of an uncontrolled trial in knee OA patients [24], assuming that our control group (without exercise training) would not improve over time while awaiting TKR. It is also assumed that the effect size is reasonable, in the sense that an effect of this magnitude could be anticipated in this field of research. Alpha has been set at 0.05 and the power has been set at 0.9. In each group 25 patients are needed.

Assuming a drop-out rate of 12%, we will include 40 patients per group.

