### Analysis plan

All analyses are based on intent-to-treat, including all randomized individuals who had at least 1 intervention session. We will use linear regression to evaluate the effect of our training program plus knee school against knee school alone for both the primary and secondary endpoints – after the training and at 3 months after surgery. The multivariate analyses for the primary endpoint (Chair Stand Test) and secondary endpoints (pain and function subscales of the KOOS) will control for baseline function of the respective endpoint, age in years, gender, and baseline body mass index. To account for the reduced exposure time to the training intervention for participants who were on a short waiting list or were less adherent we will perform subgroup analyses by training exposure groups (we will use the median as a cut-off for lower and higher intensity of the training program based on number of training sessions attended).

To evaluate a benefit of the training program on patient-reported pain and function across all time points, we will use repeated measures linear regression analyses controlling for baseline strength/function, time, age, gender, and body mass index.

Analyses will be conducted with R version 2.14.1 software. All P values are two-sided.

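### The primary Chair Stand Test is tested both before surgery and 3 months after it, with no rule for which result decides the trial, and the power calculation supports only the pre-surgery comparison

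*Protocol article*

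**What the plan says.** The Hypothesis section, under its primary endpoint, expects the training group to perform the Chair Stand Test faster "immediately after the intervention and after TKR surgery". The Design section schedules the primary endpoint at two assessments after baseline: "1 week pre-operative (after the intervention: primary and secondary endpoints") and "3 months after surgery (primary and secondary endpoints"). Table 1 marks the Chair Stand Test at the same two visits.

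The Analysis plan applies linear regression to the primary and the secondary endpoints "after the training and at 3 months after surgery". The repeated-measures model described there is for patient-reported pain and function, so it does not combine the two Chair Stand comparisons into one test. P values are two-sided.

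Under Sample size calculation, "The sample size calculation is based on the primary endpoint - the Chair Stand Test". One difference in change is used: 7.3 s (8.3 against 1.0) with SD 7.3 s, alpha 0.05 and power 0.9. The result is 25 per group, with 40 per group to be enrolled and 12% drop-out assumed. On its origin: "This effect was selected based on pilot data of an uncontrolled trial in knee OA patients". The controls are assumed not to improve during the wait for surgery. No effect or SD is given for 3 months after surgery.

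**The concern.** The two comparisons ask different questions. The first is whether training helps before the operation. The second is whether any gain survives an operation that both groups undergo. The article's Background describes large gains from surgery itself and calls earlier trials inconclusive after it. A split result, with benefit before surgery and none at 3 months, is therefore quite possible, and the protocol does not say whether such a trial has succeeded.

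The gap matters differently under each reading. If one significant result is enough, there are two chances to succeed and the 5% error rate is not kept. If both are needed, the error rate is kept, but the trial's power then depends on a 3-month effect that the protocol never states. With the rule left open, the reading could be chosen after the results are known.

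**Working it through.** **Inputs.** Difference 7.3 s, SD 7.3 s (standardized effect d = 1.0), alpha 0.05, power 0.9, 25 needed and 40 enrolled per group, 12% drop-out: all from Sample size calculation. Two-sided tests: Analysis plan. Evaluable per group: 40 × 0.88 = 35.2, taken as 35. The correlation between the two test statistics and the 3-month effect are not in the document. Both are assumed and shown as ranges.

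**Step 1: the plan's own figure, for one comparison.**
- Normal approximation: n = 2(1.960 + 1.282)² / 1.0² = 21.0, rounded up to 22 per group.
- Exact t test: 22.02, rounded up to 23 per group.
- 22 / 0.88 = 25, so the stated 25 may already include drop-out.

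The stated 25 is thus consistent with one comparison at d = 1.0. Power by t test is 93.4% at 25 per group and 98.5% at 35.

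**Step 2: either result counts.** Each test is taken at two-sided 0.05. If independent, familywise error = 1 − 0.95² = 9.75%. With correlated (bivariate normal) statistics:

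| Assumed correlation | Familywise error |
|---|---|
| 0 | 9.75% |
| 0.3 | 9.5% |
| 0.5 | 9.1% |
| 0.7 | 8.3% |
| 0.8 | 7.8% |

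**Step 3: both results required.** Type I error for the joint claim is at most 0.05. Joint power = P(Z₁ > 1.96 and Z₂ > 1.96), where Z₁ has mean d₁√(n/2) and Z₂ has mean d₂√(n/2). With n = 35 and d₁ = 1.0, the pre-operative mean is √17.5 = 4.18. The joint figures use the normal approximation, with correlation from 0 to 0.8; the last column is by t test.

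| Assumed 3-month effect d₂ | Joint power, 35 per group | 3-month test alone |
|---|---|---|
| 1.0 SD (7.3 s) | 97-98% | 98.5% |
| 0.75 SD (about 5.5 s) | 87-88% | 87.1% |
| 0.5 SD (about 3.7 s) | about 55% | 54.1% |
| 0.3 SD (about 2.2 s) | about 24% | 23.6% |

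The result depends almost entirely on the 3-month effect and hardly at all on the correlation. At 25 per group, with d = 1.0 at both times, joint power is about 89-91%. At 35 per group and SD 7.3 s, the smallest difference detectable with 90% power at one time point is about 5.7 s.

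**Step 4: which comparison the stated effect describes.** The pilot was in knee osteoarthritis patients, and the control premise concerns the wait for surgery. At 3 months both groups have had the operation, so that premise no longer applies. Nothing in the article carries the 7.3 s over to that visit.

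**Step 5: effect of splitting alpha.** At 0.025 per test and 35 evaluable, pre-operative power is 96.9% (t test). For 3-month effects of 1.0, 0.75, 0.5 and 0.3 SD, the 3-month test has 96.9%, 79.9%, 42.5% and 15.7%.

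**The case against.** The strongest reply is that the Hypothesis joins the two times with 'and', which reads most naturally as requiring both. Type I error is then not inflated. A reader might infer that the error rate is simply doubled. The document does not support that as a general statement, because it needs the either-counts reading together with near-independent tests. Repeated measurements of the same test in the same patients would be expected to correlate, which lowers the figure. The article also does not say that each regression is tested at 0.05. That value appears only in the sample size calculation, and applying it to each test is an inference.

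A reader might also infer that requiring both tests pulls power below 90% by itself, because 0.9 × 0.9 = 81%. The planned size does not support this. With about 35 evaluable per group each test has well over 90% power at the stated effect, and joint power is 97-98% if that effect persists. Power falls short only if the 3-month effect is smaller, on which the article is silent. Nor does the article literally call the pilot data pre-surgical. That follows from its population and the control assumption, and is reasonable but inferred.

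Finally, testing order and alpha allocation are often left to an analysis plan, which is not shown, and this article condenses the protocol. That weakens any complaint about a missing alpha split. It does not answer the main point: which result is primary belongs to the endpoint definition, and the article gives that definition at two times without saying how they combine.

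**Conclusion.** The point holds. The primary hypothesis covers two time points, the trial's success criterion is not fixed, and the power statement supports only the pre-operative comparison. If either result counts, the error rate is about 8-10% instead of 5%, assuming each test is at two-sided 0.05 and the correlation lies between 0 and 0.8. If both are required, alpha is sound, but joint power could lie anywhere from about 24% to 98% for 3-month effects between 0.3 and 1.0 SD. That range rests on assumed effects, about 35 evaluable per group, SD 7.3 s at both visits and the full 1.0 SD effect before surgery.

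It does not follow that the trial is too small for its pre-operative question. It is comfortably sized for that, even at alpha 0.025.

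**What to change.** In Hypothesis and Analysis plan, name the 1-week pre-operative Chair Stand Test as the single primary endpoint, since it is the comparison that the sample size describes. Test the 3-month Chair Stand Test second in a fixed sequence, at two-sided 0.05, confirmatory only if the first is significant. In Sample size calculation, state that the 90% power applies to the pre-operative comparison only.

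This takes about one sentence in each section and no extra patients. Familywise error for the two tests is held at 5%, and the first test keeps its full alpha. The downside is that a 3-month finding cannot be claimed if the pre-operative test fails.

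If the sponsor wants the 3-month claim to stand alone, a 0.025/0.025 split is an alternative. It keeps about 97% pre-operative power at 35 evaluable per group, but halves the alpha for each test. In that case a 3-month effect and SD should be stated and justified.

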#### Intervention group

Participants of the intervention group receive 8–24 sessions of the neuromuscular training program prior to TKR surgery depending on location of the waiting list for surgery. Participants also receive 3 sessions of the knee school starting about 4 weeks before surgery.

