### Control group

Participants of the control group receive 3 sessions of the knee school, starting about 4 weeks before surgery.

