## Discussion

This randomized controlled trial will compare the effect of pre-operative neuromuscular training plus knee school with knee school alone on lower extremity function. The feasible training program aims to improve the activity-oriented outcome measures. The knee school serves both as an addition to the training as well as an attention control strategy in the control group. As an integral part of this trial, we assess adherence to the training intervention, which will allow per protocol analyses in addition to the primary intent-to-treat analyses.

OA is a key driver of disability at older age and is the fourth most common condition in older women and the eight most common in older men [6,51]. Given the demographic development with a rising segment of the senior population, and therefore improving functionality in individuals with OA is a public health target. Our trial aims to contribute important knowledge on whether to what extend a pre-operative training among patients on a waiting list for TKR will improve their functionality before and after surgery. The interest in the effect of pre-operative interventions has increased in the last decade, which is seen by the increasing number of publications. The evidence is up to now for different reasons moderate and a conclusive answer is not yet possible [12,52].

Our trial will also contribute to evidence-based guidelines to help physicians and patients make informed decisions [53]. With respect to patient functional status, the major predictor of patient functional status postoperatively is pre-operative status [54]. It is therefore important to test the benefit of pre-operative training in patients undergoing TKR and our trial could contribute to a definition of pre-operative treatment recommendations or guidelines.

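### The planned subgroups by training sessions attended are formed after randomisation and in the training arm only, so they can suggest a dose effect where there is none; the primary comparison is not affected

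*Protocol article*

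**What the plan says.** The Analysis plan section puts the randomised comparison first, by linear regression. It then adds a further analysis because exposure to training will vary: "for participants who were on a short waiting list or were less adherent we will perform subgroup analyses by training exposure groups". The grouping rule follows: "we will use the median as a cut-off for lower and higher intensity of the training program based on number of training sessions attended".

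Three other statements bear on this rule.

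- Intervention group section: the trained participants receive "8–24 sessions of the neuromuscular training program prior to TKR surgery depending on location of the waiting list for surgery".
- Control group section: "Participants of the control group receive 3 sessions of the knee school, starting about 4 weeks before surgery". Controls have no training sessions.
- Analysis plan section, on the regression models for the primary and secondary endpoints: they "will control for baseline function of the respective endpoint, age in years, gender, and baseline body mass index".

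The text does not say which comparison the exposure groups enter (each half against all controls, or high against low within the training arm). It does not label the analysis exploratory.

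**The concern.** A subgroup analysis keeps the protection of randomisation only if membership is fixed before allocation and can be determined in both arms. Sessions attended meets neither condition. A control cannot be classed as high or low exposure, so the upper and lower halves of the training arm have no randomised counterpart.

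By the plan's own account the count has two sources. One is time on the waiting list; a longer wait also lengthens the interval between the baseline assessment and the pre-operative test. The other is adherence, which may depend on pain, health and motivation, and pain and function are what the trial measures. If either source is related to outcome, the two halves would differ even if training did nothing.

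At stake is the reading of the dose question. It is a real question here, because the planned number of sessions varies threefold. An apparent finding that more sessions work better would be easy to believe, and this split cannot support it.

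**Working it through.** **Inputs from the protocol.** Sample size calculation section: SD 7.3 s, assumed difference 7.3 s, two-sided alpha 0.05, power 0.90, 25 needed per group, 40 enrolled per group, 12% drop-out. Evaluable per group: 40 × 0.88 = 35.2, taken as 35.

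**The plan's own figure.** The protocol gives no figure for the exposure analysis. Its sample size shows that the SD and difference are read correctly: a standardised difference of 7.3/7.3 = 1 needs 22 per group by the normal approximation and 23 by the t-test. The stated 25 gives 93.4% power by the t-test, so it is adequate.

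**Inputs not in the protocol.** The correlation between sessions attended and outcome is assumed throughout. The sign is assumed too: the figures take more sessions to go with a better prognosis, and the opposite sign would reverse them.

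**Formula.** Suppose sessions correlate r with the outcome in the training arm, both roughly normal, and training has no effect. The mean outcome in each half of a median split is then shifted from the controls by about

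bias = ± SD × r × √(2/π) = ± 7.3 × r × 0.798 s,

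and high minus low is twice that. If attendance and outcome are linked only through a third factor, correlated rA with attendance and rY with outcome, then r = rA × rY.

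**Case A: sessions correlate directly with the outcome.** Unadjusted t-test, 35 per arm, training arm split 18/17, no training effect, by simulation:

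| r | Upper half (18) vs 35 controls | Rejections at nominal 5% | Lower half vs controls |
|---|---|---|---|
| 0 | 0 | 5% | 0 |
| 0.3 | +0.23 SD = 1.7 s | about 12% | −0.24 SD |
| 0.5 | +0.38 SD = 2.8 s | about 26% | −0.40 SD |

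The formula gives 0.3 × 0.798 = 0.24 SD and 0.5 × 0.798 = 0.40 SD. The upper half is slightly less biased because it includes the median patient. For high against low, the rejection rate is about 28% at r = 0.3.

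**Case B: the link runs only through a partly prognostic factor.**

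- rA = rY = 0.3: 7.3 × 0.09 × 0.798 = 0.5 s against controls, about 6% rejections.
- rA = rY = 0.5: 7.3 × 0.25 × 0.798 = 1.46 s. Simulation gives 1.4 s and about 10% rejections with 18 against 35.
- rA = rY = 0.5, regression with 40 per arm, adjusted for four baseline covariates unrelated to the factor: +1.5 s for the upper half, −1.4 s for the lower half and 2.9 s for high against low, with 21.7% rejections for high against low.

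**Case C: training helps everyone equally.** With a constant 7.3 s benefit and the adjusted setting of case B (rA = rY = 0.5), the upper half shows 8.8 s and the lower half 5.9 s. This is an apparent dose-response with none present.

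**The whole-arm comparison.** With no training effect it showed no bias and rejected in 4.5% to 5.5% of runs in every scenario. The split is what produces the error.

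**The case against.** The strongest reply is that this is an additional analysis. The randomised comparison comes first, and the Discussion section places other analyses after it: adherence is assessed, "which will allow per protocol analyses in addition to the primary intent-to-treat analyses". A reader might infer that a confounded comparison replaces the randomised one, or that the trial's main result is compromised. The documents do not support that. The primary comparison does not use the split. (The condition of at least one intervention session for the analysis set is a separate matter.)

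Second, the size is assumed. The direct-correlation figures treat attendance as related to the outcome itself, in an unadjusted test. The planned models adjust for baseline function, age, gender and body mass index, which removes confounding through those variables. Part of the variation in sessions comes from the waiting list, which may be only weakly prognostic. All of this stands, and it is why the size is given as a range down to zero. Adjustment still cannot be relied on, because waiting time and post-baseline drivers of attendance are not in the model.

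Third, a reader might extend the criticism to the per-protocol analysis, supposing it compares adherers with all controls. The article names that analysis but does not define its population, so there is nothing in the text to criticise.

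Fourth, a reader might expect a spurious subgroup result to go straight into treatment recommendations. The Discussion says only that the trial could contribute to them, and it links this to the benefit of training as such, not to exposure groups.

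It might also be said that an unseen analysis plan could settle the matter. It could add caveats, but the article already fixes the variable, the cut-off and the purpose, and the weakness lies in these.

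**Conclusion.** The point holds for the exposure subgroups and goes no further. Grouping by attended sessions cannot do what the plan asks of it, which is to account for reduced exposure: the groups are formed after allocation, exist in one arm only, and mix waiting time with adherence. This follows from the text and needs no assumption.

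The size does need assumptions. For the upper half against controls with no training effect, it runs from about zero (attendance driven only by non-prognostic scheduling), through about 1.4 to 1.5 s (a shared factor correlating 0.5 with both), to 1.7 s with about 12% rejections (sessions correlating 0.3 with the outcome itself). It is larger for stronger correlations, and high against low shows about twice the difference. Against the assumed effect of 7.3 s these biases are modest, but they are large enough to create a dose gradient that is not there. The primary intent-to-treat result is not in question.

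**What to change.** 1. For the exposure question, record planned waiting time (or the number of sessions it would allow) at or before randomisation in both arms. Test the arm-by-planned-waiting-time interaction in the planned regression model, preferably with waiting time as a continuous variable. The Design section times the baseline assessment at 6–12 weeks before surgery, so at least an approximate date seems to be known by then, but the article does not say so and this needs confirming.
2. Keep the split by sessions attended as description only. State that it is not protected by randomisation and will not be used to claim a dose effect.
3. An instrumental-variable estimate with arm as instrument may be added, described for what it is. Controls have no training sessions, so the estimate is essentially the intent-to-treat difference divided by the mean number of sessions attended. It rescales the effect per session, assuming linearity, and does not test dose-response.

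The cost is one recorded date, a change of wording, and limited power. With 40 per group, no drop-out and a half-and-half split on waiting time (20 per cell), the standard error of the interaction is 7.3 × √(4/20) = 3.3 s, twice the 7.3 × √(2/40) = 1.6 s of the main comparison. At 90% power the detectable interaction is (1.96 + 1.28) × 3.26 = 10.6 s, more than the whole assumed effect, so a null interaction should not be read as showing that exposure does not matter. A positive one would show that benefit varies with planned wait, which need not be due to session number alone.
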